**Fig. 2 Fig2:**
[figure not shown]
PICUstars bundle elements and educational tools

**Table 2 Tab2:** Instruments and measures used to assess implementation feasibility and success (adapted from PUN et al.) [16]

**Instrument**	**Target population**	**Study phase**	**Outputs**
Empathic 30-AUS questionnaire	Parents of eligible children	From phase 2 onwards	Family engagement and satisfaction
PICU Liberation knowledge and perceptions questionnaire	PICU staff	Phase 2, 3 and 4	Drivers, barriers, knowledge gaps
Organisational readiness questionnaire	PICU staff, organisational leadership teams	Phase 2, 3 and 4	Drivers, barriers, leadership effectiveness, culture and employee morale or satisfaction/meaning making
Daily Goal checklist	PICU staff	Phase 3	Proportion of Liberation goals set
Check-in Audit	PICU staff	Phase 3	Drivers, barriers, knowledge gaps
Measure	**Definition**	**Study Phase**	**Outputs**
Feasibility	≥ 75% bundle compliance (daily goals set) at 1 year	Phase 3	Control charts of bundle compliance
Bundle fidelity (bundle compliance): Compliance with daily patient screening for PICU Liberation program using the daily goals checklist; eligible bundle element performed per patient day	≥ 75% absolute and/or ≥ 25% improvement from baseline compliance rate of checklist completion	Phase 3	Control charts of liberation goals set and bundle element activities performed per eligible patient day
Bundle performance	impact of bundle on process and quality of care (the practices that the bundle was designed to influence)	Phase 3	Complete performance is measured by a patient-day in which every eligible element of the bundle was performed (i.e., 100% of the bundle versus anything less) and “proportional performance” as the percentage of eligible elements a patient received on a given day (i.e., “bundle dose”). This will be measured only if the patient was in the PICU for a full 24 h (Table 4)

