E – Early mobility and rehabilitation	Guide to achieving mobility activities that were higher than active range of motion (i.e., dangling at edge of bed, standing at side of bed, walking to bedside chair, marching in place, walking in room or hall)	• A structured early mobilisation and rehabilitation program is commenced 24 h post admission to PICU. Children are classified into graded activity levels (Lizard, Koala, Wombat, Kangaroo) based upon the early mobilisation algorithm considering safety issues. • Assessment of physical function is completed by a paediatric physiotherapist, using the Children’s Chelsea Critical Care Physical Assessment tool (cCPAx) [30]	Instances of • Graded activity level goals set as daily goal, • Instances of mobility level sign on patient’s door • Mobility activities administered per patient per day • Mobility levels achieved: Lizard – immobile, routine positioning and range of motion unless contraindications; Koala – in bed activities including sitting; Wombat – in bedspace activities including mobility out of bed/standing; Kangoroo – mobility out of bedspace including ambulatory* • Falls Immobility Deconditioning (assessment of physical function by instances of Children’s Chelsea Critical Care Physical Assessment tool (cCPAx) Empathic questionnaire results (carers' perception of child’s mobility management)

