E	Only days when patient was not classed as “lizard – for range of motion activities only”	≥ 1 Mobility activity administered that was higher than range of motion	Mobility goal (Lizard – passive range of motion unless contraindicated; Koala – in bed activities including sitting; Wombat – out of bed activities including transfers; Kangaroo – activities away from bedspace including ambulatory) set
F	Only days when family was present	Family member/carer educated on the PICU Liberation bundle and/or participated in at least one of the following: liberation goal setting, cares, neurodevelopmental or early mobility activity, rounds, plan of care.	Suitability of family inclusion in liberation goal setting, cares, neurodevelopmental or early mobility activity, rounds, plan of care.
G	All days	Nutritional assessment tool used OR weight obtained	Nutritional goal set
H	All days	Tool to help personalise the patient for the clinicians administered OR humanism activity administered	Humanism goal set
Baby Liberation	Only infants	“flower” tool to adapt each bundle element to include developmentally appropriate components	Baby Liberation goals documented

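### Element E (mobility) drops days classed Lizard, a class the programme itself assigns, so the score can rise without more mobilisation

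*Protocol article*

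**What the plan says.** Table 4 (Phase 4) gives each bundle element an eligibility rule and a performance criterion. For element E:

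- **Eligible days:** "Only days when patient was not classed as" Lizard, the level for range-of-motion activity only.
- **Performed if:** "≥ 1 Mobility activity administered that was higher than range of motion".
- **Daily-goal column:** Lizard is one of the goals that can be set: "Mobility goal (Lizard – passive range of motion unless contraindicated".

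Table 3 (Phase 2), in the PICU Liberation column, says how the class arises: "Children are classified into graded activity levels (Lizard, Koala, Wombat, Kangaroo) based upon the early mobilisation algorithm considering safety issues". The Measures column of the same row uses the same word as a result: "Mobility levels achieved: Lizard – immobile, routine positioning and range of motion unless contraindications".

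Table 2 builds the summary measures on eligibility. Control charts show "bundle element activities performed per eligible patient day". Proportional performance, or bundle dose, is "the percentage of eligible elements a patient received on a given day". A patient-day is complete when all of its eligible elements were done.

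Under Impact measures, the Statistical analysis section says that process-of-care outcomes will be assessed before and after implementation.

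**The concern.** One label does two jobs. It decides whether a day counts for element E, and it is also the worst value of what element E is meant to measure. Two days with the same care, neither with activity above range of motion, are scored differently: a failure if the child is classed Koala, and no entry at all if classed Lizard.

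An upward line on the element E control chart therefore has two possible explanations: more children were mobilised, or more days were classed Lizard. Nobody has to act in bad faith for the second. A change in case mix or in how the algorithm is applied is enough.

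At stake is how the mobility part of fidelity and bundle performance is read. Phase 4 uses fidelity to decide whether elements should be modified, and the study is meant to produce a toolkit for other hospitals.

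**Working it through.** The plan states no rate for element E, so there is no figure to reproduce. The check turns the definitions into arithmetic.

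**Inputs.** N = scored patient-days; P = days with at least one activity above range of motion; L = days classed Lizard. The document gives none of these. Assumed: N = 100; P = 30, 40 or 50; L varied. Actual mobilisation is held fixed, and Lizard days are drawn only from days without activity above range of motion, as the label implies.

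**Element E under Table 4** = P / (N − L).

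| L | P = 30 | P = 40 | P = 50 |
|---|---|---|---|
| 0 | 30.0% | 40.0% | 50.0% |
| 20 | 37.5% | 50.0% | 62.5% |
| 30 | 42.9% | 57.1% | 71.4% |
| 40 | 50.0% | 66.7% | 83.3% |

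At P = 40, L = 60 gives 40/40 = 100%. Over all scored days, P / N stays at 30%, 40% or 50% whatever L is.

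**Proportional performance.** On a day with k eligible elements, all done except E, the score is (k − 1)/k. With k = 6 (the five all-day elements A, C, D, G and H, plus E) this is 5/6 = 83.3%. With k = 11 (every row of Table 4) it is 10/11 = 90.9%. Classing the day Lizard makes it 100%.

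**Complete performance.** Assume that the other elements are all done on half of the days, independently of E. The complete share is 0.5 × (P + L)/N. At P = 40 it is 20% when L = 0 and 50% when L = 60.

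**Opposite direction.** Element E falls only if days that did have activity above range of motion are classed Lizard: at P = 40, moving 10 such days gives (40 − 10)/(100 − 10) = 33.3%. That contradicts the meaning of the label.

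**Which meaning of the class?** The daily-goal column of Table 4 suggests a level set in advance; Table 3 also lists Lizard as a level achieved. On the second meaning, every eligible day reached Koala or higher and so had activity above range of motion. Element E is then P/P, close to 100% by construction.

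**Before versus after.** The levels appear only in the PICU Liberation column of Table 3, and in Phase 2 staff are not instructed in the programme. If Before days carry no label, all of them count. With P = 40 throughout and an assumed 30 Lizard days afterwards, element E goes from 40/100 = 40% to 40/70 = 57.1%, a gain of 17.1 points from the label alone (12.9 points at P = 30; 21.4 at P = 50).

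**The case against.** The best defence is that the class is not a free label. It follows an algorithm that considers safety, and Table 4 restricts eligibility for other elements too (B1 to B3 by sedation or ventilatory support). Some exclusion is legitimate, and the algorithm is not shown, so the room for discretion cannot be judged. This stands, and it is a reason to keep the eligible-day figure. It does not make that figure sufficient alone, because its denominator still moves with the class.

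The second defence is that Table 3 already collects mobility activities per patient per day, levels achieved and immobility, and the control charts are to draw on Table 3. A careful reader could then see more Lizard days with flat activity. This also stands and makes the remedy cheap. But Table 4 defines performance without those measures, and nothing ties them to the element E line.

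Third, Table 2 places bundle performance in Phase 3, and the explicit pre/post comparison in Phase 4 is of complication rates. The Statistical analysis section does plan before/after process measures, but does not say that they use the Table 4 ratio. The comparability problem is therefore conditional: it arises if element E is compared across periods.

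A reader might infer four stronger points, which the document does not support:

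- **That reclassifying days carries the unit past a 75% success mark.** The 75% marks in Table 2 are worded for daily goals set and for checklist completion. The bundle performance row has no threshold.
- **That the least mobile days vanish from bundle dose.** Only element E leaves the denominator on a Lizard day; the other eligible elements still score.
- **That element F is inflated in the same way.** It is eligible "Only days when family was present", but the programme does not assign presence, and the greater presence expected in the Discussion enlarges that denominator.
- **That staff will relabel children to look better.** An unblinded bedside nurse records performance, and selected compliance measures are displayed live. This makes an incentive plausible, but element E is not named among those displayed and nothing shows that relabelling occurs.

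**Conclusion.** The point holds as a defect in a stated definition. Under Table 4, more Lizard days raise element E, and through it proportional and complete performance, without more mobilisation. This follows from the definitions, given that Lizard days have no activity above range of motion. If the class means the level achieved, the measure carries almost no information. A before/after comparison of element E lacks a common denominator because no Before-period equivalent of the class is stated.

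The size is unknown. The percentages above are illustrations on assumed rates. The consequence is a possibly misleading fidelity trend for mobility, not a wrong trial conclusion. The change is worth making because it is cheap.

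**What to change.** 1. State in Table 4 that the class is the level assigned before the scored 24 hours, not the level achieved during them.
2. Keep the eligible-day figure. Beside it, report element E as the proportion of all scored patient-days with at least one activity above range of motion, computed the same way in the Before, Intermediate and After periods.
3. Show the percentage of Lizard days on the same control chart.
4. Use the all-days figure for any before/after comparison of mobilisation.

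The cost is one clarifying sentence and two extra chart lines, from measures that Table 3 already plans to collect; Phase 2 already plans a baseline method for activity levels. The all-days figure will be lower and will include some children who could not be mobilised, which is why the eligible-day figure stays beside it.

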**Fig. 3 Fig3:**
[figure not shown]
Interventions pre- vs post-Implementation of PICU Liberation (PICUstars)

During Phase 4, each bundle element will be continuously adapted based on feedback and feasibility assessment following the initial roll-out to improve usability. As a proof of concept for wider adoption in other centres, we will embed evaluation metrics within each of the educational formats provided. All the measures that reflect patient outcomes, patient and parent experience, and compliance will be collected, monitored, and communicated to staff well beyond the implementation period to ensure ongoing adherence to the PICU Liberation bundle.

### Statistical analysis

#### Sample size

The study follows a prospective before-after hybrid trial-and-implementation approach, whereby efficacy data will be collected in a convenience sample of 1800 patients (estimated) and implementation and process data will be collected from PICU staff and parents over the three-year period.

This relatively large sample of 1800 instances of complete or partial bundle implementation effects will allow an in-depth analysis of the methods considering the relatively large heterogeneity of the study population.

#### Data collection

Data will be collected for the periods of before (pre-implementation), intermediate (during implementation, 12 months in), and after (post-implementation) as well as continuously through all study phases. Data collection will include bundle feasibility, impact and implementation measures as well as clinical data. (Tables 1, 2, 3, 4).

#### Descriptive statistic analyses

The twelve pre-implementation-months will be collated and presented as a single timeframe; all months during the implementation period will be described separately. Categorical variables will be described as counts (percentage). Continuous variables will be described by their median (interquartile range). Continuous outcome measures such as the length of stay (LOS) and hospital free days will be analysed using either survival analysis and competing-risks regression. The availability of recorded data on a specific characteristic will be described (e.g., we can only describe sedation on days which had any sedation data recorded).

In addition to analysis of the whole patient cohort, we will undertake sub-analyses for patients < 6 months of age, PICU stay shorter than 48 h and non-ventilated patients.

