### Implementation process

#### Phase 1: bundle adaptation to Australian PICU context

##### Objectives

To adapt the ICU Liberation A2F bundle to PICU through identification of specific requirements for children necessitating special consideration within the A2F bundle elements. To account for further neuroscientific developmental stages, each bundle element will then be adapted for infants ≤6 months of age in the “Baby-Liberation” program.

Activities:Comparison of current practice and Liberation model of care to identify gaps and areas for improvement required. Current assessment tools and documentation will be workshopped, and results will inform the development of the nurse-led, interdisciplinary PICU Liberation model of care.Comprehensive review of the current clinical assessment tools, guidelines and documentation (e.g., pain assessment, sedation assessment) to identify and remove duplicates, and to add updated and evidence-based assessment tools and guidelines where needed.A series of focus groups and workshops to discuss and gather feedback on the acceptability of the PICU Liberation bundle elements (see Fig. 2), and the proposed education tools developed by the PICU Liberation program implementation group.Assessment of any specific bundle requirement for use in specific patient cohorts; for example, neonates and infants less than 6 months of age.Regular assessment and revision (when appropriate) of the adapted PICU Liberation elements and contents will occur. A feedback and evaluation process will be established and include clinician and family feedback, audits, and evaluations (Table 2). Survey analyses and feedback from experienced clinicians that will be engaged to help improve each bundle element based on learnings from “provide care as required” will inform changes required as well.The four study phases will include parent/carer and clinician engagement workshops.Ongoing modifications to the PICU’s Clinical Information System to streamline documentation, to add assessment pieces where required for new content (e.g., early mobility assessment), and ensure all documentation is purposeful for clinical decision-making.

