#### Phase 2: pre-implementation assessment

##### Objectives

To identify barriers and facilitators for the PICU Liberation program; to assess organisational readiness and parent satisfaction with current care practice; to collect baseline data of primary and secondary outcomes.

Activities:Assess barriers and facilitators for the PICU Liberation program using mixed methods, including targeted questionnaires, focus and expert group feedback.Assess knowledge and perception (acceptability) of the PICU Liberation bundle by staff as well as level of engagement of PICU clinicians.Assess organisational readiness (including teamwork and collaboration) and resource availability for implementing the PICU Liberation program (including education and training group activities, unit specific requirements including ability of the electronic medical record system to capture goals, and organisational readiness including culture and acceptability of concepts including inclusion of parents at ward rounds and other systems, settings and processes).Assess consumer engagement strategies and communication materials, ward round tools.Assess staff wellbeing (including retention).

To limit the Hawthorne effect, PICU staff will not be actively notified of the study during this time, nor will they be instructed on PICU Liberation [18]. Methods to measure baseline rates of correct assessments for pain, level of sedation, delirium, and occurrence of PICU related complications will be established (covering activity levels, over-sedation, withdrawal, delirium, PICU acquired weakness, ventilator free days, VAP, CLABSI, immobility, CAUTI, falls, mediation errors, PICU readmission, accidental line removal) (see Table 3).

**Table 3 Tab3:** A2F bundle [16] vs PICU LIBERATION bundle element specifics and measures (adapted from PUN et al. where able) [16]

Bundle element	Adult A2F bundle	PICU LIBERATION bundle	Measures

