C – Choice of sedatives	PAD guidelines - agitation/sedation assessments using a valid and reliable instrument.	Institutional analgesia and sedation guidelines – • Discourage use of sedatives, only second-tier treatment in the management of an agitated, ventilated patient; benzodiazepines, chloralhydrate and ketamine discouraged unless clinically indicated • Assessment of sedation, agitation or arousal recommended at least fourth hourly, using the Richmond Agitation and sedation scale (RASS) [29]	Instances of • RASS assessments/ opportunities • Sedation goal set/ opportunities • Sedation titration performed appropriately/ opportunities • Number of patients with “deep sedation” (RASS > − 2) • Instances of PTSS • Medication side effects recorded (opioids, benzodiazepines, ketamine, chloral hydrate) • Medication errors recorded • CLABSI and CAUTI • Accidental line removal Sedative use (by number of classes of sedatives used e.g., Benzodiazepines, chloralhydrate, ketamine) Empathic questionnaire results (carers' perception of child’s sedation management)
D – Early assessment and management of delirium	PAD guidelines - delirium assessments using a valid and reliable instrument	Institutional delirium checklist and guideline – • Guide to non-pharmacological (encouraged as first option) and pharmacological delirium management strategies. • Delirium assessment recommended at least daily, using the CAP-D^38^	Instances of • CAP-D assessments/opportunities, • Delirium identified (instances), • Appropriate management plan followed/opportunities (instances of non-pharmacological interventions targeting delirium, instances of pharmacological interventions targeting delirium) • sleep adjuncts utilised (e.g. day/night routine; swaddling/nesting) Empathic questionnaire results (carers' perception of child’s delirium prevention management)

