#### Phase 4 - assessment of the feasibility of A2F bundle adaptation and the implement success of the PICU liberation program

##### Objectives

Assess feasibility, adherence, acceptability, and impact of pilot study roll-out including on PICU related complications.

Activities:Assess the feasibility of adapting the A2F bundles in PICU.Measure bundle fidelity (i.e. bundle compliance/adherence), using both quantitative analytic and qualitative methods (Table 2, Table 4). If a low degree of fidelity of certain PICU Liberation bundle elements is present, or concerns regarding fidelity are identified, modifications to the bundle elements will be considered to maintain the bundle integrity and primary objective of the PICU Liberation program, i.e., improve patient outcomes.Compare PICU-related complication rate between from pre- (before period) and post-implementation (intermediate and after periods, refer to Fig. 3).Conduct focus groups to ascertain learnings from the implementation process and gather feedback from PICU staff about successes and areas for improvement to inform further adaptation, if required.

**Table 4 Tab4:** Definitions of PICU Liberation program: Bundle Performance and Daily Goals (adapted from PUN et al.) [16]

Element	Days eligible	Performance in the last 24 h it was documented that the patient received	Performance in the last 24 h it was documented on the daily goal checklist
A	All days	≥ 6 pain assessments using the FLACC assessments [26, 27]	FLACC goal
B1	Only days when patient received continuous or intermittent sedation	A spontaneous awakening trial (SAT) if receiving continuous or intermittent sedative infusions OR sedation target set as “light” in the daily goals	Suitability for SAT if receiving continuous or intermittent sedative infusions OR suitability for sedation goal set as “light”
B2	Only days when patient was on ventilatory support	A spontaneous breathing trial (SBT) if receiving invasive ventilation	Suitability for SBT if receiving invasive ventilation
B3	Only days when patient was on ventilatory support	An extubation assessments if receiving invasive ventilation	Suitability for extubation assessments if receiving invasive ventilation
C	All days	≥ 6 agitation-sedation assessments using the RASS (Richmond Agitation-Sedation Scale [29]	RASS goal
D	All days	≥ 1 delirium assessments using the CAP-D [31]	CAP-D requested

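### Sedation is described only on days with sedation recorded, and the bundle is built to change that recording, so a before/after comparison on recorded days can be biased in either direction

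*Protocol article*

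**What the plan says.** Under Descriptive statistic analyses, the article commits to reporting how complete the data are: "The availability of recorded data on a specific characteristic will be described". Its example is sedation: "we can only describe sedation on days which had any sedation data recorded". The article does not say whether sedation data means RASS scores, sedative drug records or both.

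Elsewhere it describes an intervention that changes sedation recording:

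- Table 4, element C, counts a day as performed when there are "≥ 6 agitation-sedation assessments using the RASS" in 24 hours, and lists all days as eligible. Table 3 recommends RASS at least every four hours.
- Table 2 sets the fidelity target at "≥ 75% absolute and/or ≥ 25% improvement from baseline compliance rate of checklist completion". The measure also covers eligible elements performed per patient-day.
- Phase 1 includes continuing changes to the clinical information system "to streamline documentation, to add assessment pieces where required for new content".
- In Phase 2, "PICU staff will not be actively notified of the study during this time, nor will they be instructed on PICU Liberation". The same section plans "Methods to measure baseline rates of correct assessments for pain, level of sedation, delirium" and lists over-sedation among the complications measured at baseline.

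Phase 4 compares complication rates between the Before period and the later periods. Table 3 names the number of patients with deep sedation as a measure. The Impact measures section plans absolute and relative risks and adjusted logistic regression for dichotomous outcomes.

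**The concern.** This is more than ordinary missing data, because the intervention includes the act of recording. Before-period days with a sedation entry reflect whatever the unit's usual charting picks out. Later days with an entry reflect a programme that asks for scoring on every day. Table 1 admits any child staying at least 24 hours, and non-ventilated patients are a planned sub-analysis. The cohort therefore probably contains many days on which nobody had a reason to score sedation before the bundle.

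If those days differ in depth from the recorded ones, the described population shifts between periods and the sedation result shifts with it, even when care has not changed. A reader could then take a documentation effect for a bundle effect, or miss a real one.

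**Working it through.** The article gives no deep-sedation rate, recording rate or sedation effect, so there is no figure of its own to reproduce. Every rate below is an assumption, and the true share is the same in both periods.

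**1. Deep share of recorded days.** Let π be the true share of days that are deep, and r_D and r_L the chances that a deep or a lighter day has any sedation data. Then

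observed share = π·r_D / (π·r_D + (1−π)·r_L).

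With π = 20%:

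| Before r_D / r_L | After r_D / r_L | Observed Before | Observed After | Apparent risk ratio |
|---|---|---|---|---|
| 90% / 50% | 95% / 90% | 0.18/0.58 = 31.0% | 0.19/0.91 = 20.9% | 0.67 |
| 80% / 60% | 90% / 85% | 0.16/0.64 = 25.0% | 0.18/0.86 = 20.9% | 0.84 |
| 70% / 60% | 90% / 90% | 0.14/0.62 = 22.6% | 20.0% | 0.89 |
| 50% / 50% | 95% / 95% | 20.0% | 20.0% | 1.00 |
| 60% / 70% | 90% / 90% | 0.12/0.68 = 17.6% | 20.0% | 1.13 |

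The fourth row matters: recording nearly doubles and there is no bias, because it is unrelated to depth.

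Other inputs show the same pattern. With π = 30% and 95% recording of all days After, Before rates of 80%/50% give 0.24/0.59 = 40.7% falling to 30.0% (ratio 0.74). Rates of 50%/80% give 0.15/0.71 = 21.1% rising to 30.0% (ratio 1.42).

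**2. Patients ever recorded deep.** This is closer to the measure named in Table 3. Over D independent days the chance is 1 − (1 − π·r_D)^D. With π = 30%, D = 5, and recording of deep days rising from 60% to 95%:

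- Before: 1 − 0.82^5 = 62.9%
- After: 1 − 0.715^5 = 81.3%

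This is an apparent worsening with no change in care.

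**3. More scores within a recorded day.** Suppose a day counts as deep on any deep score, and 10% of scores are deep, independently. The chance is 1 − 0.9^2 = 19% with two scores and 1 − 0.9^6 = 47% with six. This also pushes towards apparent worsening.

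**4. What bounds would show.** If a fraction r of days is recorded and a share p of those is deep, the share over all days lies between p·r (no unrecorded day deep) and p·r + (1 − r) (all deep). In the first row of the table:

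- Before, 58% recorded: 18% to 18% + 42% = 60%
- After, 91% recorded: 19% to 19% + 9% = 28%

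The true 20% lies in both intervals, and they overlap, so the spurious ratio of 0.67 would not be read as a finding. In general, an observed 30% is compatible with 15% to 65% at 50% recording, 24% to 44% at 80%, and 28.5% to 33.5% at 95%.

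**The case against.** The recorded-days wording is a parenthetical example in a descriptive section, attached to a promise to report availability. The effect analysis under Impact measures does not repeat the restriction. No charting pattern is given for the Before period. The text asks only for any sedation data on a day, so moving from one or two scores to six does not change which days are included. Weighting and bounds are details that a separate analysis plan may hold, and the article already names missing data as a threat under Methodological limitations.

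Much of this stands. Depth-related recording is an inference, and the bias is zero without it. The absence of a full missing-data method is not the point here. What remains is that the article itself fixes the recorded-days basis, while the bundle changes which days are recorded. The adjusted regression is described as dealing with prognostic factors, not with recording. The missing-data remedies offered are data-capture measures. The any-data threshold helps only where days already had an entry, and step 3 shows that extra scores can still matter.

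A reader might infer that the selection must favour the bundle and produce a false improvement in sedation. The documents do not support that. Row five of the table reverses the direction, and the patient-count measure tends to look worse as recording rises.

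**Conclusion.** The concern holds as a risk of bias of unknown direction in the before/after sedation comparison. It rests on one assumption that the article does not state: that recording depends on sedation depth. With π = 20% and the assumed rates shown, no true change appears as a risk ratio between about 0.67 and 1.13. Stronger or weaker selection widens or narrows that range, and recording unrelated to depth gives 1.00. A count of patients ever recorded deep tends to rise. Reporting availability reveals the difference between periods but does not correct for it.

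Sedation is one of many measures and is not named as primary, so this limits what can be concluded about sedation rather than undermining the study. It is worth changing because a distortion of this size could be mistaken for an effect and the remedy is cheap.

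**What to change.** For the before/after sedation comparison:

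1. Use all eligible patient-days as the denominator, and show unrecorded days as their own category by period and ventilation status. State what counts as sedation data.
2. Give bounds that set unrecorded days to all deep and to none deep.
3. Add a sensitivity analysis that weights recorded days by the inverse probability of being recorded, for example from age, ventilation, sedative infusion, day of stay, diagnosis and severity. This helps only as far as those variables explain recording, which is why the bounds are also needed.
4. Claim a change in sedation only where it survives these analyses; otherwise report it as descriptive.

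Do not make ventilated or sedative-infusion days the main comparison. The bundle aims to change both, through awakening and breathing trials, nurse-enabled extubation and discouraging sedatives, so conditioning on them would bring in a new selection. They can serve as a supportive analysis.

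Two practical points. The bounds cover unrecorded days, not extra scores on recorded days, so show the number of scores per recorded day by period as well. Table 3 also prints deep sedation as RASS > −2, which literally selects scores above −2, and this must be reconciled before any depth comparison.

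The cost is revised analysis wording, a little more analysis work and a wider, less favourable sedation result. If Before-period recording is low, the bounds may not exclude no change at all.
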